## Methods

### Study design and setting

For the proposed study, we will use an open-label cluster-randomized trial of 24 randomly chosen villages (*n* = 12 intervention and *n* = 12 control) in Kampala (*n* = 15), Wakiso (*n* = 3), Mukono (*n* = 4), and Masaka (*n* = 2) districts. Intervention and control villages are located at least 20 km apart to avoid contamination

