(iv) Baseline data collection: At baseline, trained research assistants will collect demographic (age, gender, education level and place of residence) information and administer the Mental health Knowledge Schedule (MAKS) [36] to assess for MHL, Kesler-10 (K-10) [37] to measure PD, the Generalized Anxiety Disorder scale (GAD-7) [38] to assess for GAD, Patient Health Questionnaire-9 (PHQ-9) [39] to assess for MDD, Post-Traumatic Stress Disorder-Primary Care Screen (PTSD-PC) [40] for PTSD, and the Alcohol Smoking and Substance Involvement screening Test (ASSIST) [41] to assess for SUD. This data will be collected from participants in both arms. During the baseline data collection, the IEC materials will be distributed to participants in the intervention arm and the ministry of health (MOH) brochures to participants in the control arm.

(v) The intervention: VHTs will distribute the IEC materials to the 12 intervention villages described above after collection of baseline data and encourage participants to read these materials. In the 12 control villages, VHTs will distribute the MOH brochures that contain information about (a) the signs and symptoms of the COVID-19 and the preventive measures, (b) the fact that individuals may suffer from stress during the pandemic, (c) the sources from where they can get psychosocial help, and (d) the contact details of the research team should they need more information. The information contained in the ministry of health brochures are the current standard of care for community members. The IEC materials will be distributed to individuals who participated in the baseline surveys.

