(vi) Mitigating the possibility of contamination between the study arms: Being an educational intervention, it is not possible to blind the participants in the control villages from receiving information meant for those in the intervention arm. Thus, there is a chance that participants in the control villages will access IEC materials distributed to those in the intervention arm, leading to contamination of our findings. To avoid contamination, we will do the following: (i) randomize villages so that they are at least 20 km apart (with the limited human movements during the COVID-19 pandemic, we anticipate that there will be little by way of people sharing the IEC materials), (ii) conduct the assessments within a week of distributing the materials to limit the chances that the information will be widely circulated, and (iii) ask participants in the control arms if they accessed the IEC materials meant for the control group—we will document the number of individuals who fall in this category. We have no control of other educational interventions that may be instituted during the trial period and circulated using the mass media. However, these interventions are usually sanctioned by the MOH—we are already working with the MOH and will know the nature and extent of these interventions if any. In the event that individuals are provided with similar information, then we will find out how many of them received it and acted on them. However, the trial period is quite short (7–10 days) and we believe that we can engage the MOH to implement these interventions after our intervention is complete.

(vii) Follow-up data collection: The same trained RA’s will collect follow-up data within a week after the VHTs have distributed IEC materials. The RA’s will administer the instruments administered at baseline (MAKS, K-10, GAD-7, PHQ-9, PTSD-PC, and ASSIST). The RA’s who collected the baseline data will be the same ones to collect the follow-up data. They would have set up appointments for the follow-up interview and will know the terrain well enough. The time duration between baseline and follow-up is a week. However, in some situations where the participant cannot be accessed within the week, we will give an allowance of up to 4 weeks within which to conduct the follow-up interviews—should the participant not be available within the said 4 weeks, then we will consider them as lost to follow-up.

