To estimate the number of villages required per arm for a clinically important effect size of 50%, we assume power of 80% at the 95% confidence level, mean MHL score of 14.14 and standard deviation (SD) of 2.19 [42], and cluster size of 35 participants and coefficient of variation of 0.25, which yields ~ 8 villages per trial arm. Therefore, 24 villages (both arms) will be required, thus including up to 840 participants (420 per trial arm). The sample size of 24 clusters with 35 participants in each cluster will provide us with enough power to detect statistically significance difference between the two arms.

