### Statistical analysis

Objective 1: We will report frequencies and percentages of the study outcomes and their 95% confidence intervals. We will use regression analyses to determine associations between the primary outcome (MHL) and the factors that may be associated with it (demographics, CMD).

Objective 2: An intention-to-treat analysis will be conducted to compare the groups at baseline and within 4 weeks to assess the effects of the intervention on MHL. We will use a Student t test to examine this difference. The dependent variable (MHL) will be calculated as a continuous variable. Independent variables including presence of PD, MDD, GAD, PTSD, or SUD will be presented as continuous and categorical variables. Baseline characteristics of the intervention and control arms will be compared at the 5% level to assess if successful randomization was achieved. Data on potential confounders and effect modifiers, including variables that fail to achieve successful randomization (e.g., socio-demographic parameters) shall be used to control for confounding and effect modification. Between-subject analysis at week 4 will be used to assess the direct effect of the intervention by determining if there is a significant difference between the mean MHL scores in the intervention and control arms. Within-subject analysis will be performed among participants in the intervention arm by applying the Generalized Estimating Equations method on repeated measures data.

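### Testing baseline differences at 5% cannot show whether randomisation worked, and using the result to choose covariates makes the adjusted estimate partly data-driven

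*Protocol article*

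**What the plan says.** All of this stands in the Protocol article.

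- Statistical analysis, Objective 2, sets the test and its purpose: "Baseline characteristics of the intervention and control arms will be compared at the 5% level to assess if successful randomization was achieved".
- The next sentence ties the result to the model. It describes the set of variables for adjustment as "including variables that fail to achieve successful randomization (e.g., socio-demographic parameters) shall be used to control for confounding and effect modification". The verb is mandatory for flagged variables. No covariate is fixed in advance.
- The between-arm test named for MHL has no covariates: "We will use a Student t test to examine this difference". No test is named for the baseline comparisons, and nothing says that they will account for villages.
- Study procedure gives the variables that could be tested. There are four demographic items, "demographic (age, gender, education level and place of residence) information", and six scales, which are repeated at follow-up: "The RA’s will administer the instruments administered at baseline (MAKS, K-10, GAD-7, PHQ-9, PTSD-PC, and ASSIST".
- The design is an "open-label cluster-randomized trial of 24 randomly chosen villages".

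**The concern.** Two things are wrong with the rule as written.

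First, the test does not answer the question put to it. If villages were allocated properly, any baseline difference produced by the allocation is chance, and a small p-value is a chance event. If participants were recruited differently in the two arms, that is a recruitment problem and not a failure of randomisation. If the test treats people in the same village as independent, it rejects too often. The protocol would read all three results as unsuccessful randomisation.

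Second, the significance of an imbalance is the wrong reason to adjust. What makes a covariate useful is how well it predicts the outcome. A baseline p-value is silent on that. Baseline MAKS or education could predict follow-up MHL strongly and still show no significant imbalance, while a variable unrelated to MHL could be flagged and forced into the model.

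At stake are an adjusted effect estimate whose covariates depend in part on the baseline data of this one trial, and a published statement that randomisation failed when it did not.

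**Working it through.** **The plan's own figures.** The protocol gives no false-flag rate, so there is none to reproduce. The nearest stated figure is the number of villages: "we assume power of 80% at the 95% confidence level", with "cluster size of 35 participants and coefficient of variation of 0.25, which yields ~ 8 villages per trial arm". With means 14.14 and 1.5 × 14.14 = 21.21, SD 2.19, m = 35 and k = 0.25, the Hayes–Bennett formula gives

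c = 1 + (1.96 + 0.84)² × [2 × 2.19²/35 + 0.25² × (14.14² + 21.21²)] / 7.07² = 7.42,

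which rounds up to 8, as stated. I do not take k as a guide to clustering in the baseline variables: 0.25 × 14.14 = 3.54 is a between-village SD larger than the stated SD of 2.19.

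**Inputs for the check**

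- Variables: 4 demographics + 6 scales = 10, each tested once (Study procedure).
- Level: 5% (Statistical analysis), taken as two-sided.
- Clusters: 24 villages of 35, 12 per arm.
- Clustering of baseline variables: not given. I assume an intracluster correlation (ICC) of 0 to 0.10. The protocol's design effect of 2 belongs to the prevalence-survey sample size. Carried over as an assumption, it implies ICC = (2 − 1)/34 = 0.029.
- Correlation between variables: not given. I assume 0 to 0.5.
- No true difference between arms and no selective recruitment.

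**Tests that respect villages.** For independent variables, P(at least one flag) = 1 − 0.95^K.

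- K = 4 (demographics only): 18.5%
- K = 10: 40.1%
- K = 13: 48.7%; K = 14: 51.2%

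I simulated ten variables tested on village means, with 1,500 runs per setting. This gave 38.5–40.7% with no correlation and 28.5–30.9% at pairwise correlation 0.5. Hence about 29–40%.

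**Tests that ignore villages.** The design effect is DEFF = 1 + 34 × ICC. The true error rate per test is 2 × [1 − Φ(1.96/√DEFF)]. At DEFF = 2 this is 2 × [1 − Φ(1.386)] = 16.6%, and 1 − (1 − 0.1658)^10 = 83.7%.

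| ICC | DEFF | Error per test | ≥1 flag of 10, independent | ≥1 flag of 10, correlation 0.5 (simulated) |
|---|---|---|---|---|
| 0.01 | 1.34 | 9.0% | 61% | 47% |
| 0.029 | 2.00 | 16.6% | 84% | 68% (run at ICC 0.03) |
| 0.05 | 2.70 | 23.3% | 93% | 82% |
| 0.10 | 4.40 | 35.0% | 99% | 94% |

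**Count of variables.** Place of residence is largely fixed by village and does not share these per-test rates. Without it, nine independent variables give 1 − 0.95^9 = 37.0% for valid tests and 1 − (1 − 0.1658)^9 = 80.4% at DEFF = 2. The picture is the same.

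**The case against.** Four points can be made for the protocol.

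- **The adjustment set is open.** The sentence says that flagged variables are included among the confounders, not that they are the only ones. Nothing excludes an unflagged predictor, and a full covariate list may sit in an analysis plan that is not shown. This stands. A reader might infer that covariates are chosen only by the test and that baseline MAKS and education will be left out; the text does not say so. It supports only that they may be omitted. The complaint here is about a stated rule, not a missing list.
- **The named test is untouched.** The Student t test for MHL does not change with the baseline flags. This also stands. The rule affects the adjusted analysis, and the protocol does not say which estimate is primary.
- **Baseline MAKS may already be used.** The primary outcome under Study outcomes is a change in MHL. That is partly right, but a change score is not the same as adjusting for baseline. The Statistical analysis section also describes a comparison of mean scores at week 4, which would not use baseline at all.
- **Baseline differences here need not be chance.** The trial is open-label, and village health teams are contacted before they help to find people willing to take part. If allocation is known by then, recruitment could differ by arm. This is a fair reason to inspect baseline data. It does not rescue a 5% test, which cannot tell this cause from the others.

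**Conclusion.** The point holds as a criticism of the stated rule. Baseline significance tests should neither judge the randomisation nor decide which variables enter the adjustment.

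With about ten variables, the chance of at least one spurious flag is about 29–40% if the tests respect villages. It is about 68–84% if they ignore them at a design effect of about 2. The lower ends assume pairwise correlation 0.5, which is plausible because several scales measure related distress; the upper ends assume independence. The design effect is borrowed from the survey calculation, and the other ICC values are assumptions.

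A reader might infer that the 5% rule alone would declare failed randomisation in most trials like this one. The documents do not support that. With valid, independent tests the chance passes 50% only from 14 variables. Most trials would show a flag only if the tests also ignored villages with enough clustering. That is a natural reading of a section that names a t test and no cluster term, but the protocol does not state it for the baseline comparisons. Nor does the result reach every effect estimate: only the adjusted one depends on the flags.

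**What to change.** In Statistical analysis, Objective 2:

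1. Delete the 5% baseline comparisons and the rule that flagged variables are added to the adjustment.
2. Say instead that baseline characteristics will be shown by arm, as means with SDs or as counts with percentages, without p-values.
3. Name the adjustment covariates before data are seen: at least baseline MAKS, plus demographics already collected, such as age, gender and education. Apply them in whatever between-arm model is used; the choice of that model is a separate matter.
4. If an imbalance in an unlisted variable looks large, report a sensitivity analysis that adds it, labelled as such.

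I would not make district a required covariate on this point alone. Masaka contributes 2 villages and Wakiso 3, and no stratification by district is described, so a small district could fall wholly in one arm.

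The change costs a few sentences and needs no new data or participants. The small downside is that a chance imbalance in an unlisted variable would be handled only in the sensitivity analysis.

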### Study outcomes

Our primary outcome will be a mean change in MHL between the two arms. The secondary outcome will be associations between the MHL and demographic and CMD variables assessed by way of regression analysis.

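### The repeated-measures GEE is confined to the intervention arm, so the change it estimates cannot be separated from retesting or outside messages and is not evidence of effectiveness

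*Protocol article*

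**What the plan says.** The relevant text is in the Statistical analysis section of the protocol article, Objective 2. Its aim is to "compare the groups at baseline and within 4 weeks to assess the effects of the intervention on MHL", and it names the test: "We will use a Student t test to examine this difference". It then gives two analyses in succession.

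- Between arms: "Between-subject analysis at week 4 will be used to assess the direct effect of the intervention". This compares mean MHL scores in the two arms.
- Within one arm: "Within-subject analysis will be performed among participants in the intervention arm by applying the Generalized Estimating Equations method on repeated measures data". No purpose is given for this analysis, and it is not marked as descriptive.

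Three other places bear on it.

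- Study outcomes: "Our primary outcome will be a mean change in MHL between the two arms".
- Study procedure (iv) collects the baseline scales in both arms. Item (vii) repeats them, with the same research assistants, who "will administer the instruments administered at baseline (MAKS, K-10, GAD-7, PHQ-9, PTSD-PC, and ASSIST"). On timing it says "The time duration between baseline and follow-up is a week", with an allowance of up to four weeks.
- Study procedure (vi), on outside messages: "We have no control of other educational interventions that may be instituted during the trial period".

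**The concern.** A before-after change in a single arm has no comparator. Here it contains at least three components: the effect of the materials, any gain from answering the same Mental health Knowledge Schedule (MAKS) twice about a week apart, and any effect of messages that reach participants from outside the trial. The model as described cannot separate them.

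The control arm has the same two measurements and could remove the last two components, but it is left out. The only model named for repeated measures therefore does not estimate the stated primary outcome, which is change between arms. What is at stake is interpretation: a significant rise in the intervention arm could be presented beside a null between-arm result as support for the intervention.

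**Working it through.** **What the plan gives.** It states no figure for the GEE, so none can be reproduced. The inputs come from the section Sample size and statistical considerations: mean 14.14, SD 2.19, 35 participants per village, coefficient of variation 0.25, 420 participants per arm (12 villages × 35). The plan's figure from these inputs does reproduce. With the Hayes-Bennett formula, 80% power, two-sided 5% (assumed) and a 50% rise to 21.21:

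1 + (1.96 + 0.84)² × [2 × 2.19²/35 + 0.25² × (14.14² + 21.21²)] / (21.21 − 14.14)² = 7.42, rounded up to 8 villages per arm.

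That neither supports nor weakens this point.

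**Assumptions not in the documents.** Correlation ρ between baseline and follow-up MHL, 0.3 to 0.7; ICC of change, 0 to 0.05; a gain g common to both arms; no intervention effect; full follow-up of 420 per arm.

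**Standard error of the within-arm mean change.**

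- SD of change = 2.19 × √(2(1 − ρ))
- Design effect = 1 + 34 × ICC
- SE = SD of change × √(design effect / 420)

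At ρ = 0.5 and ICC = 0, SE = 2.19 × √(1/420) = 0.107 points.

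**Rejection rate of the one-arm test.** Village-level test on 12 villages, non-central t with 11 degrees of freedom and non-centrality g/SE:

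| ρ | ICC of change | SE | g = 0.25 | g = 0.5 |
|---|---|---|---|---|
| 0.3 | 0 | 0.126 | 44% | 95% |
| 0.3 | 0.05 | 0.208 | 20% | 59% |
| 0.5 | 0 | 0.107 | 57% | 99% |
| 0.5 | 0.05 | 0.176 | 26% | 74% |
| 0.7 | 0 | 0.083 | 79% | 100% |
| 0.7 | 0.05 | 0.136 | 39% | 92% |

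At g = 1.0 the rate is at least 99% throughout. A gain of 0.5 points is 0.5/2.19 = 0.23 SD. The one-arm estimate equals g, so all of it is bias as a measure of the intervention.

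**Two-arm comparison of change.** In 5,000 simulated trials per setting (ρ = 0.5; ICC 0, 0.02 and 0.05; g from 0 to 1.0; t with 22 degrees of freedom), it rejects in 4% to 6% of trials, with mean bias about 0. The common gain cancels.

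**A small gain, 0.1 SD = 0.219 points.** Here the result is fragile:

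- ρ = 0.5, ICC 0: z = 0.219/0.107 = 2.05, p = 0.04
- ρ = 0.3, ICC 0: z = 0.219/0.126 = 1.73, p = 0.08
- ρ = 0.5, ICC 0.05 (design effect 2.7): z = 0.219/0.176 = 1.25, p = 0.21

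**The case against.** The strongest reply is that this GEE is an extra. The sentence before it gives the role of effect estimate to the between-arm comparison at week 4, the primary outcome is defined between arms, and nothing says the GEE result will be reported as effectiveness. That stands, and it limits the consequence. Several stronger readings are tempting, but the text does not support them.

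- A reader might infer that the GEE result will be taken as the intervention effect. The document does not say so. The risk comes from its place under an objective about the intervention's effects, with no descriptive label.
- A reader might infer that the plan discards the randomised comparison. It does not: only this model omits the control arm.
- A reader might infer that no other analysis uses both time points. The t test sentence mentions baseline and follow-up together and can be read as a test of change, although it does not say so.
- A reader might infer that the GEE clusters on the participant and ignores villages. The clustering unit is not stated, and an article may leave it to a fuller document.

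Outside messages are also not wholly unmanaged. The same part of Study procedure says they usually have Ministry approval, that the team works with the Ministry and expects to know of them, that recipients will be counted, and that the trial period is short. This makes a large outside effect less likely. It does not put a comparator into the one-arm model, and it does nothing about retesting.

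Finally, no size for a retest gain comes from the documents, and a gain of 0.1 SD is not reliably significant. That also stands.

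**Conclusion.** The point holds as a defect of one analysis. The within-arm GEE cannot distinguish the materials from retesting or outside messages, omits control data that the trial collects, and does not match the primary outcome. The between-arm week-4 comparison is not biased by gains common to both arms, so the trial keeps a valid contrast on this score.

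On the assumed ranges for correlation and ICC, an assumed common gain of 0.5 points with no intervention effect gives a significant one-arm result in roughly 59% to 100% of trials, against about 5% for a two-arm comparison of change. At 0.1 SD, z runs from about 1.2 to 2.05 when the correlation (0.3 to 0.5) and the ICC (0 to 0.05) are varied one at a time, so no firm statement can be made there. These figures show the mechanism. They do not forecast the gain in this trial.

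**What to change.** Replace the one-arm GEE with a repeated-measures model fitted to both arms, with arm, time and arm × time terms, and report the interaction as the between-arm effect on change in MHL. Account for village, either by using village as the GEE cluster with a small-sample corrected variance for 24 clusters, or by a mixed model with random effects for village and participant. State that within-arm changes are descriptive only and are not evidence of effectiveness.

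The cost is a change of wording in the analysis section. Both measurements are already planned in both arms, so no new data, visits or participants are needed.

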### Data safety management board

The data safety management board (DSMB) will be comprised of [name] (psychiatrist and senior epidemiologist), [name] (pharmacologist and IRB member), and [name] (clinical psychologist with vast experience in conducting RCT) from Makerere University. The PI will have periodic meetings with the DSMB and provide them with reports about the study activities using an agreed template. There will be at least two meetings during the study period one at the beginning and another midway through the study. Members of the DSMB will make a visit at the Butabika Hospital where data will be stored. During this visit, the study procedures (SOPs and manuals), study responsibilities (delegation log), site facilities (data room), study materials (stationary and administrative materials), and the recruitment and retention plan will be discussed.

